### Study outcomes and measurement of study variables

The study outcomes will be measured after the completion of the intervention implementation. The primary outcome of this study is - increase in instrumental agency of MAGs in decision making regarding SRHR (i.e., FP use; timing of first conception; and number of children to have). Table 2 presents the primary and secondary outcomes to be measured among different target groups.

**Table 2. Different outcomes to be measured among different target groups of Balika Bodhu**

| Sl                        | Outcome                                                                                                                                  | MAGs | Husbands of MAGs | Community members |
|---------------------------|------------------------------------------------------------------------------------------------------------------------------------------|------|------------------|-------------------|
| Primary outcome    |                                                                                                                                          |      |                  |                   |
| 1                         | Instrumental agency of MAGs in decision making regarding SRHR (i.e., FP use; timing of first conception; and number of children to have) | √    |                  |                   |
| Secondary outcomes |                                                                                                                                          |      |                  |                   |
| 2                         | Intrinsic agency of MAGs                                                                                                                 | √    |                  |                   |
| 3                         | Instrumental agency of MAGs                                                                                                              | √    |                  |                   |
| 4                         | Collective agency of MAGs                                                                                                                | √    |                  |                   |
| 5                         | Critical consciousness (perceived inequality, egalitarianism and critical action) regarding gender inequality in the society             | √    |                  |                   |
| 6                         | Knowledge of MAGs regarding FP and conception                                                                                            | √    |                  |                   |
| 7                         | Positive attitudes of MAGs regarding FP and conception                                                                                   | √    |                  |                   |
| 8                         | Couple communication initiated by MAGs regarding FP use, timing of first conception, and number of children to have                      | √    |                  |                   |
| 9                         | MAGs attempts to negotiate FP use, timing of first conception, and number of children to have as per her choice                          | √    |                  |                   |
| 10                        | Service uptake among MAGs regarding abortion and post-abortion care, and help seeking after experiencing violence                        | √    |                  |                   |
| 11                        | Prevalence of intimate partner violence (IPV) among the MAGs                                                                             | √    |                  |                   |
| 12                        | Knowledge of husbands of MAGs regarding FP and conception                                                                                |      | √                |                   |
| 13                        | Positive attitudes of husbands of MAGs regarding FP and conception                                                                       |      | √                |                   |
| 14                        | Positive attitudes regarding agency of MAGs regarding SRHR among the husbands                                                            |      | √                |                   |
| 15                        | Non-condoning attitudes of husbands of MAGs regarding violence against women                                                             |      | √                |                   |
| 16                        | Positive attitudes of husbands of MAGs regarding gender roles within household                                                           |      | √                |                   |
| 17                        | Knowledge of community members regarding FP and conception                                                                               |      |                  | √                 |
| 18                        | Positive attitudes of community members regarding FP and conception                                                                      |      |                  | √                 |
| 19                        | Positive attitudes regarding agency of MAGs regarding SRHR among the community members                                                   |      |                  | √                 |
| 20                        | Positive attitudes of community members regarding violence against women                                                                 |      |                  | √                 |
| 21                        | Positive attitudes of community members regarding gender roles within household                                                          |      |                  | √                 |
| 22                        | Positive social norms regarding SRHR of MAGs                                                                                             | √    |                  | √                 |

**Instrumental agency of MAGs in decision making regarding SRHR (i.e., FP use; timing of first conception; and number of children to have)**

The MAGs will be asked about the main decision maker regarding: (a) FP use; (b) timing of first conception; and (c) number of children to have. The response options included '1=the MAG herself', '2=husband', '3=jointly' and '4=someone else'. A follow up question, 'what kind of joint decision it was', was asked if the response was 'jointly'. The response options included '1=he voiced his choice and I agreed', 'he voiced choice and forced me to agree', and '3=I voiced my choice and he agreed'. A MAG will be considered agentic in decision making regarding a specific theme of SRHR and will be coded as 'Yes=1' if she decided herself or it was a joint decision without any force on her, and 'No=2' otherwise. We will generate a summative score, with a higher score indicating higher agency.

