#### ***Inclusion and exclusion criteria for individual participants***

##### Inclusion criteria

Criteria for inclusion of the MAGs in the study will be: i) adolescent girls aged 15-19 years; and ii) currently married and living with husband; and iii) both the girl and her husband have no intention of migrating out within the next 15 months. The husbands of the selected adolescent girls will also be included in the study. Community members aged 35-59 years will also be considered eligible for participating in the study.

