### **Intimate partner violence (IPV)**

MAGs' experience of IPV (i.e. controlling behaviour, and physical and sexual violence IPV) will be measured using a modified version of The Revised Conflict Tactic Scale (Straus et al., 1996). The scale is the most widely used measure of IPV which is characterized by having direct and behaviorally explicit questions in order to reduce variation in the interpretation and understanding of what violence comprises of. These instruments are designed to minimize reporting biases that arise from subjective perceptions of abuse by asking only about specific behaviours perpetrated by a male partner (e.g., "Has your husband or any other family member ever slapped you or threw something at you that could hurt you?"). Questions will capture behaviours that reflect minor and severe physical violence (e.g., slapped, pushed, hit with a fist, kicked, dragged, choked, burned, threatened with a weapon); and sexual violence (e.g., forced sexual intercourse or other sexual acts). To measure economic coercion, we will use a modified version of the ECS-20 (Yount et al., 2022). Typical items include—your husband or any other family member ever and in last 12 months: disallowed you to go to your work, school or training, or do any home-based income earning activity; told that you could work outside the home only if you kept up with the housework; told that you could earn income only if you worked from home; etc. A woman will be considered exposed to any specific type of IPV if she responds "yes" to any of the items related to that specific type of IPV, and will be coded "yes=1", and "no=0" otherwise.

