## **Ethical considerations**

The study will seek ethical approval from icddr,b's institutional review board. Informed consent will be obtained from the study participants. Participation in the study will be as entirely voluntary. Individual verbal consent will be sought by the interviewer prior to the interview with each study participant. The MAGs who are minor (aged below 18) will be considered as "mature minors" and following the guidelines for adolescent health research published by the National Commission for the Protection of Human Subjects of Biomedical and Behavioral Research and the Society for Adolescent Medicine (Society for Adolescent Medicine, 2003; National Commission for the Protection of Human Subjects of Biomedical and Behavioral Research, 1977) we will seek informed consent from them.

According to English et al., (1995), mature minors are those who are living apart from their parents, married, pregnant, parents themselves, and self-supporting and they are allowed to give consent (English et al., 1995). In our study, we will consider MAGs aged below 18 as "mature minors" as all of them are married and some of them are expected to be pregnant and/or have child/ren. Thus, the mature minors in this study do not require consent from a guardian.

The primary ethical purpose of obtaining consent of a guardian is to ensure that vulnerable children are protected from potential risks a research may pose. However, this approach does not always protect a minor (National Commission for the Protection of Human Subjects of Biomedical and Behavioral Research, 1977), and may be problematic in some situations as well (Department of Health and Human Services, National Institutes of Health, Office for Protection from Research Risks, 2001). Examples of such situations, where parental permission is not appropriate and is not a reasonable requirement include, abuse, contraception use, etc.). Most of the MAGs will be living not with their parents, but with their husbands and in-laws, usually considered as their guardians. Since our study deals with sensitive issues such as sexual and reproductive coercion and violence, where the most common perpetrators are the husbands it would be unethical to leave it up to them to decide whether or not the girl will participate in the study. Informing the potential perpetrator about the study may also increase the risks of abuse of the girls. Due to these ethical concerns consent must not be obtained from the husbands.

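### One of the three items in the primary score cannot be changed by the programme in girls who conceived before baseline, and the scoring rule makes no provision for them

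*Protocol*

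**What the plan says.** The primary outcome is described below Table 2: "MAGs will be asked about the main decision maker regarding: (a) FP use; (b) timing of first conception; and (c) number of children" to have. A domain counts as agentic if the girl decided herself, or jointly without force. Then: "We will generate a summative score, with a higher score indicating higher agency". The three items are therefore equally weighted. No recall window is given, the follow-up question on joint decisions is phrased in the past tense, and no rule covers a girl whose first conception already lies behind her.

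The Inclusion criteria ask for "i) adolescent girls aged 15-19 years; and ii) currently married and living with husband", together with no plan to migrate. Neither they nor the exclusion criteria mention pregnancies or births. Ethical considerations says of the girls under 18 that "all of them are married and some of them are expected to be pregnant and/or have child/ren", and the application form ticks pregnant women as a special group.

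The programme lasts 12 months, nobody is blinded, and Quantitative data analyses compares change from baseline between the arms.

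Secondary outcomes 8 (communication started by the girl) and 9 (attempts to negotiate) use the same three themes, so they also include timing of first conception.

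On violence (outcome 11), the example of a physical item reads "Has your husband or any other family member ever slapped you or threw something at you that could hurt you". Economic coercion is asked both for ever and for the last 12 months. The coding rule is: "A woman will be considered exposed to any specific type of IPV if she responds" yes to any item of that type. Neither that section nor Table 2 says which window defines the outcome.

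**The concern.** A first conception that precedes baseline is a completed event. The programme can affect what a girl decides next about contraception or family size, but not who decided something that has already happened. In these girls item (b) can change only through recall or a new way of describing the past. Intervention girls know their arm and attend sessions on rights, negotiation and first conception. A difference between arms on this item among them would therefore be differential reporting, not an effect on decisions.

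Two things are at stake. The primary score becomes less sensitive to a real effect, by an amount that depends on a share the protocol does not state. And part of any observed effect could be re-description of the past, which the scoring rule cannot separate from real change.

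For violence, the risk is similar but conditional. If lifetime items feed the endline variable, a girl exposed before baseline stays a case whatever happens during the programme. Counting acts by other relatives also sits badly with the section's own description of the instrument, which speaks of acts by a male partner.

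**Working it through.** **1. The protocol's own sample size.** Inputs, from Sample Size Calculation: 50% against 65%, 5% significance (taken as two-sided), 80% power, 22 girls per cluster, ICC 0.05.

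- Individual randomisation: 170 per arm.
- Design effect: 1 + (22 − 1) × 0.05 = 2.05.
- Clusters per arm: 170 × 2.05 / 22 = 15.84, so 16. This agrees with the protocol; power at 16 clusters is 80.6%.
- Inflation for losses: 22 / (0.85 × 0.80 × 0.90) = 35.9, against the stated 35. 35 × 32 = 1,120.

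This calculation is for a binary outcome on FP use, conception and SRH service uptake, not for the three-item score. Its 15 points can therefore serve only as an illustrative effect per item.

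**2. Dilution of the score.** Let d be the true effect on each item wherever the item can still change, and f the share of girls who conceived before baseline. Items are taken as scored 1/0, in line with the stated direction of the score and the recoding to a zero anchor.

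- Full effect on the sum: 3d.
- Effect with item (b) fixed in a share f: 2d + (1 − f)d = (3 − f)d.
- Ratio: (3 − f)/3 = 1 − f/3, whatever the value of d.

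With d = 0.15 the full effect is 0.45 on the 0–3 score. The protocol gives no f, so these values are assumptions:

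| f | Score effect | Loss (f/3) |
|---|---|---|
| 20% | 0.420 | 7% |
| 30% | 0.405 | 10% |
| 50% | 0.375 | 17% |
| 70% | 0.345 | 23% |
| 80% | 0.330 | 27% |

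**3. What this could mean for power (illustration only).** Suppose the score had exactly 80% power at full effect, with unchanged variance. With k = 1 − f/3, power becomes Φ(k × (1.96 + 0.84) − 1.96), and the sample needed to restore 80% is multiplied by 1/k².

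| f | k | Power | Sample multiplier |
|---|---|---|---|
| 30% | 0.900 | 0.71 | 1.23 |
| 50% | 0.833 | 0.65 | 1.44 |
| 70% | 0.767 | 0.57 | 1.70 |

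The protocol does not state the power of the score. In an analysis of change, an item answered identically twice also adds no variance, so the real loss of power may be smaller. The f/3 loss in the effect itself is unaffected.

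**4. The same effect under a proportion of applicable domains.** A girl never pregnant at baseline contributes 3d/3 = d; a girl with an earlier conception contributes 2d/2 = d. The expected effect is d for any f, against d(1 − f/3) when the present sum is divided by 3.

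**5. Violence, passages side by side.** The example physical item is lifetime, the coercion items carry two windows, and the coding rule accepts a yes to any item without naming a window. The items name the husband or another relative, while the text describes acts by a male partner. The definition can thus be read in more than one way, and no calculation is needed to see it.

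**The case against.** The strongest reply is that the problem is bounded and unbiased by design. The ethics section says some girls, not many. Item (b) stays open to change in every girl who had not conceived at baseline. Randomisation spreads the others over both arms, so their presence does not confound the comparison. Random recall error in both arms would not create a false effect either; only a differential shift would. All of this stands, and it limits the size of the point without removing it.

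Four stronger readings are tempting but not supported:

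- **A full third of the outcome is lost.** That holds only if every girl had conceived before baseline; otherwise the loss is f/3.
- **Power falls to between 50% and 13%.** Those are the figures for item (b) tested alone at f of 30% to 70%, with 15 points at full effect. The protocol plans no such test; its outcome is the summed score.
- **Outcome 11 is a lifetime measure.** Its window is not stated, and 12-month answers are collected at least for economic coercion.
- **Outcome 11 could never show a benefit.** Even with lifetime coding, new onset among girls unexposed at baseline can differ between arms.

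It can also be said that the violence window is a matter for the statistical analysis plan. That is partly fair, and it is why the violence point ranks lower. But window and perpetrator must be recorded separately in the questionnaire, or no later plan can recover them. For the primary score, the protocol itself fixes the items, the eligibility and the summation.

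**Conclusion.** The point holds for the primary outcome. Applied as written, the scoring rule includes an item that the programme cannot truly change in girls who conceived before baseline. The effect on the mean score is reduced by f/3: 10%, 17% and 23% at an assumed f of 30%, 50% and 70%. This rests on equal effects across the three items and on a share that the documents do not report. Any difference between arms on that item among these girls would be differential reporting. The documents do not show that such a shift will occur, and the main expected harm is dilution.

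The first-conception parts of outcomes 8 and 9 have the same weakness. For outcome 11 the supportable conclusion is narrower: the time window is unstated and the perpetrator wording is inconsistent. If lifetime items feed the endline variable, only new onset can separate the arms.

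This is a worthwhile and inexpensive improvement to the sole primary outcome, not a defect that invalidates the trial.

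**What to change.** **Primary score.** Record at baseline whether each girl has ever been pregnant. Score item (b) only in girls never pregnant at baseline. Define the primary score as the number of applicable domains decided with agency divided by the number applicable: three for girls never pregnant at baseline, two for the others. Set applicability from baseline status only. This respects randomisation and keeps every girl interviewed at endline in the analysis. Use the same rule for outcomes 8 and 9.

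**What not to do.** Do not restrict the items to decisions made in the last 12 months. The programme covers first conception and birth spacing, so whether such a decision arises may depend on arm. The score would then be conditioned on a post-randomisation event.

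**Violence.** Define outcome 11 as acts by the husband in the last 12 months, which matches the length of the programme. Report lifetime acts and acts by other family members separately, and ask window and perpetrator as distinct questions.

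**Cost.** A recoding rule, one baseline status variable and small wording changes. Survey tools describes the questionnaires as still to be developed and already lists first conception and birth interval as topics. The downside is that item (b) rests on fewer girls, and girls with an earlier conception are scored on two answers instead of three, so not all of the lost precision is regained.

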### **Positive attitudes of MAGs regarding FP and conception**

Positive attitudes of MAGs regarding SRHR will be measured using six items, like 'family planning is a women's business and a man should not worry' and 'a woman has right to choose when to first conceive'. The participants will report their agreement on a Likert scale (1 = strongly agree to 4 = strongly disagree). A summative score will be obtained, with a higher score indicating more positive attitude regarding SRHR.

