**Positive attitudes regarding agency of MAGs regarding SRHR among their husbands**

Attitudes of husbands of MAGs about agency of MAGs regarding SRHR will be measured using 12 items. A typical example includes “It should be a wife’s decision when to have a child”. The participants will report their agreement on a 4-point Likert scale (1 = strongly agree to 4 = strongly disagree). A summative score will be obtained, divided into tertiles. Negatively valenced items will be reverse-coded, so higher score indicates more positive attitudes.

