### **Quantitative data analyses**

Items in the survey questionnaires will be recoded so that all are anchored at 0. For example, for gender norms and attitudes, each item with scores ranging between 1 and 4 in the questionnaire will be recoded to 0–3. Negatively valenced items will be reverse-coded, so higher score indicates positive outcome. All the measurement scales used in the study will be validated using factor analysis. This exercise will allow us as well to reduce the number of items in the scales. Internal consistency (or reliability) of a scale will be measured using Cronbach's alpha. A scale with alpha equal to 0.60 or more will be considered acceptable. Scale validity will be measured using the Kaiser-Meyer-Olkin (KMO) test, where KMO equal to 0.60 or more will be considered acceptable. Once the final scale is constructed, a summative score will be obtained for each scale, and the scores will then be divided into tertiles.

During baseline we will explore the current situation in empowerment and SRHR among MAGs and their correlates, while at end line we will measure the impact of the social norms intervention on empowerment, on social norm change and promotion of demand, access and positive practices in relation to SRHR among the MAGs. Using the baseline survey data, the basic background characteristics (e.g., age, education,

religion, ethnic group) of the girl and community samples will be compared by arm (control, treatment) to check the arm balance. Descriptive analyses will be performed to report frequencies and percentages of different outcomes of interest. Chi-square, ANOVA and t-tests will be performed to check whether the study arms are covariate balanced. Linear and logistic regression analyses will be performed to identify the underlying factors for current situation in SRHR among MAGs.

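### The primary outcome's scoring rule runs opposite to its stated direction, and the reversal rules for five attitude scales are wrong or missing

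*Protocol*

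**What the plan says.** **Primary outcome.** Below Table 2, the Protocol first lists the raw answers on who decided (four options, with a follow-up on the kind of joint decision). It then defines a derived variable for each theme (family planning use, timing of first conception, number of children). A girl "will be coded as 'Yes=1' if she decided herself or it was a joint decision without any force on her"; the rule then continues "No=2' otherwise. We will generate a summative score, with a higher score indicating higher agency".

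**General recoding rule.** The section Quantitative data analyses says "Items in the survey questionnaires will be recoded so that all are anchored at 0", with an example that moves 1–4 to 0–3. It adds "Negatively valenced items will be reverse-coded, so higher score indicates positive outcome".

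**Attitude scales.** Nine scales (Table 2, outcomes 7, 13–16 and 18–21) are coded from 1 for strong agreement to 4 for strong disagreement, and all say that higher is better. They differ in the items shown and in whether their sections state a reversal:
- *Family planning and conception (7, 13, 18).* For the girls the text is "1 = strongly agree to 4 = strongly disagree). A summative score will be obtained, with a higher score indicating more positive attitude". One example item is favourable ("a woman has right to choose when to first conceive") and the other is unfavourable (family planning as no concern of men). No reversal is stated.
- *Agency of the girls (14, 19).* The example item is favourable (the timing of a child should be the wife's decision). For husbands the rule is "Negatively valenced items will be reverse-coded, so higher score indicates more positive attitudes", and the community section says the same in substance.
- *Violence (15, 20) and gender roles (16, 21).* The example items are unfavourable. No reversal is stated.

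By contrast, the gender-equity items under Intrinsic agency run from 1 for strong disagreement to 4 for strong agreement.

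**The concern.** A summed score takes its direction from the item codes, not from the sentence that describes it. If the better answer carries the lower code, the total falls as agency rises. For the sole primary outcome, an analyst who follows the coding as written would get an effect with the wrong sign against its label.

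The attitude scales raise a related problem. Reversing the unfavourable items is the right step when agreement carries the high code, as under Intrinsic agency. These nine scales give agreement the low code, so the same step moves items away from the stated direction. If an analyst repairs some scales by judgement and leaves others, the direction of effect may differ between outcomes without any record of it.

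**Working it through.** **Planning figure.** The scoring rule has no stated numerical result to reproduce. The planning rates used below come from the sample size section: 50% prevalence, a 15% effect, intra-cluster correlation 0.05, cluster size 22, 5% significance and 80% power. Read as 50% against 65%, the usual two-proportion formula without continuity correction gives 170 per arm. The design effect is 1 + 21 × 0.05 = 2.05, and 170 × 2.05 / 22 = 15.84, so 16 clusters per arm, as stated. The 15% is therefore a 15-point difference.

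**Primary score.** With *a* agentic themes out of three, the literal sum is 1 × *a* + 2 × (3 − *a*) = 6 − *a*. Anchoring at 0 subtracts 1 per theme and gives 3 − *a*.

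| Agentic themes | As written | Anchored at 0 | With No = 0 |
|---|---|---|---|
| 0 | 6 | 3 | 0 |
| 1 | 5 | 2 | 1 |
| 2 | 4 | 1 | 2 |
| 3 | 3 | 0 | 3 |

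Anchoring is a shift and leaves the order reversed. The reversal rule does not help, because an agentic decision coded Yes is not a negatively worded item.

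**Size.** Assume that the planning rates apply to each theme. With a proportion *p* agentic per theme, the literal mean is 3 × (2 − *p*): 4.50 at 50% and 4.05 at 65%, a change of −0.45. With No = 0 the mean is 3*p*: 1.50 and 1.95, a change of +0.45.

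**Attitude items.** After anchoring, strong agreement scores 0 and strong disagreement 3. Each cell gives the score of the most favourable answer, then of the least favourable.

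| Rule | Unfavourable item | Favourable item |
|---|---|---|
| No reversal | 3, 0 (correct) | 0, 3 (reversed) |
| Reverse unfavourable items | 0, 3 (reversed) | 0, 3 (reversed) |
| Reverse favourable items | 3, 0 (correct) | 3, 0 (correct) |

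Applied to the items shown:
- *Outcomes 14 and 19:* the favourable item is left alone and scores 0 for the best answer. Reversed by their own text.
- *Outcomes 7, 13 and 18:* with no reversal the two example items cancel (best respondent 0 + 3 = 3, worst 3 + 0 = 3). Under the general rule the best respondent scores 0 + 0 = 0 and the worst 3 + 3 = 6. Neither reading gives the stated direction.
- *Outcomes 15, 16, 20 and 21:* with no reversal the best answer scores 3. Correct by their own text.

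**The case against.** The intended direction is never in doubt: the primary outcome and all nine attitude scales say that higher is better. Elsewhere the Protocol codes derived yes/no variables 1 and 0 (knowledge, negotiation, partner violence). For couple communication it lists raw options 1 and 2 and then gives a 1/0 recode. The No = 2 code may well be a questionnaire code carried over by mistake, and an analyst would probably notice. Factor analysis and Cronbach's alpha might also expose scales whose items pull in opposite directions. Only one or two items per scale are shown, so the direction of the rest is unknown.

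Most of this stands, and it limits the point. It does not remove the primary-outcome error. The raw answers are listed separately, so Yes = 1 and No = 2 is the stated rule for the derived variable. Alpha and the Kaiser-Meyer-Olkin measure would not flag a scale that is reversed throughout, and dividing a score into tertiles would keep the reversal.

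A reader might infer that all nine attitude scales are reversed. The documents do not support that. The violence and gender-role scales are correctly directed on the items shown. They go wrong only if the general reversal of negative items is applied to them mechanically, against the aim stated in the same sentence. A reader might also infer that a benefit will be reported as harm. That would require applying the codes literally while ignoring the direction stated beside them.

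**Conclusion.** The primary outcome's scoring rule is wrong as written: the sum falls from 6 to 3 as agency rises, and anchoring at 0 does not change that. It should be corrected before any analysis. The ±0.45 illustration rests on applying 50% and 65% to each of the three themes; the Protocol gives one planning rate, not one per theme. If the three-theme score is also cut into tertiles, as the analysis section says for scales, a raw mean difference may not be the reported estimate, though the order would still be reversed.

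Of the nine attitude scales, two are reversed on the item shown, three show opposing items that neither the section text nor the general rule resolves, and four are sound on the item shown. This is a contradiction between codes and stated direction, not a forecast of inverted results. The sample size does not depend on it.

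**What to change.** 1. In the primary outcome definition, code an agentic decision 1 and any other decision 0, so that the sum runs from 0 (none) to 3 (all themes).
2. For scales coded from 1 for strong agreement to 4 for strong disagreement, reverse the favourably worded items and leave the unfavourable ones. Alternatively, re-anchor these items to 1 for strong disagreement, as under Intrinsic agency, and keep the present reversal rule.
3. Make the general rule in Quantitative data analyses agree with whichever option is chosen, and list the direction of every item for each scale.

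The cost is wording and recode syntax. The sample size and the design are unaffected.
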